#### 2.12.1 Mediation analyses

Mediation will be evaluated using path models. Of key interest are the total effect (sum of all paths between clinical severity rating at baseline and 12-month follow-up), the direct path between clinical severity rating at baseline and 12-month follow-up, and the indirect path (total-direct) via key demographic variables (e.g., age, gender), personality and social participation factors. Statistical inference will be based on the nonparametric bootstrap if the assumption of normality is violated.

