## 2. Materials and methods

### 2.1 Objectives

The main aim of this study is to evaluate the clinical efficacy and cost utility of an augmented psychological CBT intervention for treating anxiety and/or depression in older adults. We will compare this augmented psychological intervention, which will incorporate a targeted focus on increasing social participation (enhanced CBT), with the current best practice transdiagnostic CBT program (standard CBT) for older adults with anxiety and/or depression [16, 17]. To evaluate the efficacy of the enhanced CBT program, the inclusion criteria for study participants will be selective; participant adherence will be closely monitored through clinician supervision, and the clinicians delivering treatment will be specially trained in the intervention and its application. The intervention will be conducted in our research laboratory and the risk of other confounding interventions (e.g., concurrent treatments) will be limited. The enhanced CBT program has the potential to increase recovery rates for older adults suffering from depressive and anxiety disorders, enhance wellbeing and social participation in this age group, and improve economic outcomes for payers and society. The results of this study could improve the efficacy of psychological interventions for late-life anxiety and depression, in a way that offers value-for-money and could be considered for public financing. In addition, we will examine the underlying moderators of treatment response, and changes in cognitive functioning over time.

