In addition to the primary and secondary outcome measures, the **Personality Inventory for DSM-5—Brief Form** [PID-5-BF; 34] will be used to undertake a mediation analysis on treatment outcomes. The PID-5-BF is a 25-item self- rated personality trait assessment scale for adults aged 18 years and older. It assesses five personality trait domains including negative affect, detachment, antagonism, disinhibition, and psychoticism, with each trait domain consisting of five items.

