### 2.12 Statistical methods

Data will be analysed using intention-to-treat principles. All participants will be included in analyses based on the condition to which they were initially allocated. Multiple imputation will be used to manage missing data. The efficacy of the programs will be established using mixed model analysis to compare the mean differences in clinical diagnostic severity (established by clinicians who are blind to treatment allocation) and scores on self-report measures at pre-treatment, post-treatment, and at a 12-month follow-up period.

Analysis will be a mixed model with random subject effect, fixed effects relating to group allocation (between-group), time (within-subject) and covariates. Interaction contrasts will be used if the time x group interaction reaches statistical significance, but the main effect contrast will be used if not.

Statistical inference will be based on the nonparametric bootstrap if the assumption of Normality is violated. The same process will be used for the secondary hypotheses to compare the groups on all outcome measures. Differences between groups in baseline characteristics, and therapy factors (e.g., sessions attended, therapist alliance) will be examined and controlled for in analyses.

In addition, an economic evaluation will be undertaken to measure the relative benefit in health outcomes and resource use for the enhanced intervention compared to standard CBT. Moderation analyses will examine the impact of moderators on treatment outcomes.

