In the current study, the intervention strategies in the enhanced CBT program are designed to increase meaningful social interactions through a combination of cognitive and behavioural techniques. Research indicates that a transdiagnostic CBT program for depression and anxiety may be effective in reducing loneliness in older adults, and that this reduction is likely to be facilitated by targeting shared underlying cognitive and behavioural mechanisms between loneliness, depression, and anxiety [20]. The current study will be testing out hypotheses around the application of CBT skills in addressing these underlying mechanisms. That is, participants in the enhanced CBT program will be encouraged to actively identify and challenge unhelpful or unrealistic cognitions related to social activities and interactions. This process is complemented by behavioural activation to encourage broader engagement in social activities, including scheduling regular activities with family and friends, participating in community group activities, and/or volunteering. Participants will also be encouraged to practise graded exposure to reduce avoidance of social interactions, as well as problem solving logistical barriers (e.g., cost and transportation). Furthermore, the enhanced CBT program will focus on improving assertiveness skills and conflict management to strengthen social relationships.

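### As written, the mediation effects in section 2.12.1 start at baseline severity instead of randomised arm and treat age and gender as intermediates, so they do not estimate mediation of the treatment effect

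*Protocol article*

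**What the plan says.** All references are to the protocol article.

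- **Section 2.12.1 (Mediation analyses)** lists the quantities of key interest: "the total effect (sum of all paths between clinical severity rating at baseline and 12-month follow-up"; then "the direct path between clinical severity rating at baseline and 12-month follow-up"; then "the indirect path (total-direct) via key demographic variables (e.g., age, gender), personality and social participation factors". Clinical severity rating (CSR) is the ADIS-5 rating used for the primary outcome. Treatment arm is not mentioned in this section.
- **Section 2.6** states the purpose of the personality inventory (PID-5-BF): it "will be used to undertake a mediation analysis on treatment outcomes".
- **Section 3 (Discussion)** speaks of mechanism: "The current study will be testing out hypotheses around the application of CBT skills in addressing these underlying mechanisms".
- **Section 2.12** names allocation as a model term in the efficacy mixed model, with "fixed effects relating to group allocation (between-group), time (within-subject) and covariates". It gives moderation one separate sentence: "Moderation analyses will examine the impact of moderators on treatment outcomes".
- **Section 2.1** promises that "we will examine the underlying moderators of treatment response" but does not list the moderators.
- **Table 1** schedules the participation and connection scales (ACPQ-12, LSNS, DJGLS-11), PID-5-BF and ADIS-5 at T1, T2 and T3.

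**The concern.** A mediation analysis of a treatment effect splits the effect of arm on outcome into a part that passes through an intermediate variable and a part that does not. The quantities in section 2.12.1 split something else: the association between severity at baseline and severity at 12 months. Their indirect part would show how far later severity follows from earlier severity by way of the listed variables, in both arms together.

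The same sentence also places age and gender on the path. Both are fixed before baseline severity is measured and cannot be caused by it.

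What is at stake is the mechanism analysis. The case for the enhanced programme (sections 1.1, 2.5 and 3) is that raising social participation should improve outcome. If the section is followed as written, the trial will report an indirect effect through social participation that does not address that idea but could easily be taken to do so.

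**Working it through.** Section 2.12.1 states no figure of its own, so there is none to reproduce. The check is a comparison of the stated paths, followed by a short derivation and an illustration.

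**Step 1. Start and end of each stated quantity**

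| Quantity | Starts at | Ends at | Arm named? |
|---|---|---|---|
| Total | CSR at baseline | CSR at 12 months | No |
| Direct | CSR at baseline | CSR at 12 months | No |
| Indirect (total minus direct) | CSR at baseline | CSR at 12 months | No |

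Arm is in none of the three.

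**Step 2. What the stated indirect effect estimates**

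Let A be arm, X baseline CSR, M participation at T2 and Y CSR at 12 months, with

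- M = aA + gX + error
- Y = 0.5X + bM + c'A + error

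The effect of arm carried by participation is a × b. The quantity in section 2.12.1 (total minus direct for X, arm not in the model) is g × b when a or c' is zero, as in the three cases below. If both are non-zero, leaving arm out also distorts the M-to-Y leg. The two quantities share b, but a does not enter g × b. Randomisation makes A independent of X in expectation, so one cannot stand in for the other.

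The coefficients below are assumptions for illustration and are not in the protocol. X and the errors have unit variance. There were 4000 simulated trials of n = 172, the planned total.

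| Case | a | b | g | c' | g × b | As written: simulated mean (SD) | a × b | Arm-based: simulated mean (SD) |
|---|---|---|---|---|---|---|---|---|
| 1. Participation carries all of the arm effect; baseline CSR does not affect participation | 1 | -0.5 | 0 | 0 | 0 | 0.00 (0.043) | -0.50 | -0.499 (0.110) |
| 2. Participation carries none of the arm effect; baseline CSR affects participation | 0 | -0.5 | -0.4 | -0.5 | 0.20 | 0.200 (0.050) | 0 | 0.001 (0.077) |
| 3. Both paths present | 1 | -0.5 | -0.4 | 0 | 0.20 | 0.199 (0.052) | -0.50 | -0.498 (0.108) |

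Cases 2 and 3 give the same answer as written, although the treatment mechanism is absent in one and complete in the other. Case 1 gives zero when the mechanism is complete.

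**Step 3. Age and gender as intermediates**

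Let Z be age, Y = βX + δZ + error, and γ the slope of Z on X.

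- Coefficient of X without Z: β + δγ
- Coefficient of X with Z: β
- Total minus direct: δγ

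This is non-zero whenever age is associated with baseline severity and, given baseline severity, with later severity. Baseline severity cannot have caused age, so δγ is confounding removed by adjustment. Under section 2.12.1 it would be labelled an indirect effect.

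**Step 4. Whether an arm-based model is feasible**

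Arm is randomised. The candidate mediators are measured at T1 and T2, and CSR at T3. The order of exposure, mediator and outcome is available from the scheduled data.

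**The case against.** **The section is brief and does not exclude arm.** It lists quantities of interest, not every path, and a full analysis plan might add arm as a predictor or grouping variable. A reader might therefore infer that arm is left out of the model altogether, or that the analysis holds no information on mechanism. The document does not support either statement: arm is simply not mentioned, and the participation-to-outcome leg is common to both models. But the article positively defines the start and end of its effects. Adding arm as a covariate would not change what those effects measure, so this is a mis-stated target and not detail left to a later plan.

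**Participation as mediator of the arm effect is not a stated aim.** This is correct. Section 2.1 lists efficacy, cost utility, moderators and cognitive change. Section 2.6 ties mediation to personality, and the mechanisms in section 3 are cognitive and behavioural ones shared by loneliness, depression and anxiety. The aim is inferred from the rationale. What remains is the mismatch between section 2.6, which refers to treatment outcomes, and section 2.12.1, in which treatment does not appear.

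**Personality may be a legitimate mediator.** A reader might infer from section 2.1 that personality and demographics are meant only as moderators. Neither section 2.1 nor the moderation sentence in section 2.12 names them. PID-5-BF is measured at all three times and assigned to mediation in section 2.6, so change in traits could be an intermediate. Only age and gender are ruled out.

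**The bootstrap is already planned if Normality fails.** This is so, and the point is minor. An indirect effect is a product of coefficients and is generally skewed in finite samples even with Normal errors. How skewed it would be here depends on path strengths that the protocol does not give, and this was not calculated.

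**The simulation follows by construction.** It does. It illustrates the algebra and is not evidence on the size of any effect in this trial.

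**Conclusion.** The point stands in a limited form. All three quantities of key interest in section 2.12.1 run from baseline CSR to 12-month CSR. As written, they describe the persistence of severity and cannot deliver the mediation analysis of treatment outcomes announced in section 2.6. Listing age and gender as intermediates is a separate error, because adjustment for them would be counted as mediation.

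The conclusion is structural and rests on the wording and on randomisation, not on the assumed coefficients. That participation is the mediator of main interest is a reading of the rationale, not a stated aim.

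The consequence is confined to an ancillary analysis. The primary comparison, the other secondary outcomes, the economic evaluation and the sample size are unaffected. The change is worth making before the analysis is run, but it does not threaten the trial's main result.

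**What to change.** Rewrite section 2.12.1 as follows:

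- **Exposure:** randomised arm.
- **Mediators:** social participation and connection at T2 (ACPQ-12, LSNS, DJGLS-11). If the personality aim of section 2.6 is kept, add PID-5-BF at T2.
- **Outcome:** CSR at T3.
- **Covariates:** baseline CSR, the baseline value of each mediator, age and gender.
- **Age and gender:** covariates, or moderators in the separate moderation analysis; not intermediates.
- **Effects reported:** total, direct and indirect effects of arm.
- **Inference (minor):** bootstrap intervals for the indirect effect by default, without a prior Normality check.
- **Status:** exploratory. Randomisation protects the arm-to-mediator leg but not the mediator-to-outcome leg, which stays observational. Section 1.1 itself describes social interaction and distress as probably influencing each other in both directions.

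The cost is one rewritten paragraph. All variables and assessment times are already in Table 1, and no additional participants or data are needed.

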### 2.7 Sample size

Based on review of the available literature and our pilot study results comparing this enhanced CBT program to an active control group, we predict the enhanced CBT program to produce a controlled effect size (against standard intervention) of Cohen’s *d* = 0.5. Therefore, based on a moderate effect of Cohen’s *d* = 0.5, with power at 90% and, alpha at 0.05 (two-sided), 172 participants (86 equally randomised to each condition) in total are required, with the expectation that 15% of participants will be unsuitable based on outcomes of the baseline assessment (based on previous studies in our clinic that use a brief intake screener to determine likely eligibility into the program prior to baseline assessment), at least 200 participants will be recruited. In order to understand the representativeness of the population, demographic information will be collected with respect to sex, age, country of birth, ethnicity, education, marital status, income, employment status, living circumstances (e.g., retirement villages), pre-existing health conditions, psychiatric history (including duration), and current medications (type, dosage, and frequency) at time of intake/baseline assessment, post-treatment, and at each follow-up assessment.

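### The mediation plan bootstraps the indirect effect only if normality fails, but normal data do not make an indirect effect normal; a delta-method default could cost up to about 20 points of power, depending on path sizes

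*Protocol article*

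**What the plan says.** Protocol article, section 2.12.1: "Mediation will be evaluated using path models". Three quantities matter most there: the total effect and two paths. One path is "the direct path between clinical severity rating at baseline and 12-month follow-up". The other, which is the one at issue here, is "the indirect path (total-direct) via key demographic variables (e.g., age, gender), personality and social participation factors". The rule for inference comes next in that section: "Statistical inference will be based on the nonparametric bootstrap if the assumption of normality is violated".

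The sentence is almost word for word the rule for the mixed model in section 2.12: "Statistical inference will be based on the nonparametric bootstrap if the assumption of Normality is violated". Section 2.12.1 does not say which quantity has to be normal, and it does not name the method used when normality holds. It gives no path coefficients and no power for the mediation analysis.

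**The concern.** For a single contrast in a mixed model, normal residuals do support normal-theory inference, so a bootstrap fallback is reasonable in section 2.12. The indirect effect is a different kind of estimate. It is a product of two coefficients (or a sum of such products when there are several mediators), and a product of two normal estimates is not itself normal. The rule in section 2.12.1 therefore checks a condition that does not settle the validity of the test it governs. It withholds the bootstrap when the data are well behaved, although the indirect effect needs it there too.

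At stake is a conservative test with a symmetric interval for a skewed estimate, so that a real but modest indirect path is more likely to be reported as not shown.

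**Working it through.** **1. The plan's own figure.** Section 2.7 states "with power at 90% and, alpha at 0.05 (two-sided), 172 participants (86 equally randomised to each condition) in total are required", "based on a moderate effect of Cohen’s *d* = 0.5". By the normal approximation, n per arm = 2 × (1.960 + 1.282)² / 0.5² = 84.1, so 85. The t-test solution is 85.03, so 86, with 90.3% power at 86 per arm. The 172 reproduces. It concerns the primary comparison and says nothing about mediation.

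**2. Why normal data are not enough.** In a linear single-mediator model, total − direct = a × b, where a is the exposure-to-mediator path and b the mediator-to-outcome path. Suppose both estimates are exactly normal and independent, with standard error s ≈ 1/√172, so s² = 0.00581 and s⁴ = 0.0000338. Then

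- variance of the product = a²s² + b²s² + s⁴
- third central moment = 6ab·s⁴

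With a = b = 0.20, the variance is 0.08 × 0.00581 + 0.0000338 = 0.000499 (SD 0.0223). The third moment is 6 × 0.04 × 0.0000338 = 0.00000811. Skewness = 0.00000811 / 0.0223365³ ≈ 0.73. No departure from normality in the data has been assumed.

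**3. Why the delta-method test is conservative.** z = ab / √(a²·SE_b² + b²·SE_a²). Dividing through by SE_a·SE_b gives z = z_a·z_b / √(z_a² + z_b²), which is always smaller in size than the weaker of the two path statistics. If z_a = z_b, it equals z_a/√2, so each path must reach 1.96 × 1.414 = 2.77 rather than 1.96. With a = b = 0.20 the expected path statistic is 0.20 × √172 = 2.62, and 2.62/1.414 = 1.86 falls short of 1.96. At 0.30 it is 3.93/1.414 = 2.78, comfortably past it. If one path is strong, the penalty on the other is small.

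**4. Simulated power.** Assumed model: one mediator, normal exposure, mediator and outcome errors, direct path 0.3, N = 172, 1,000 trials per row, 600 resamples. The path sizes are assumptions.

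| a, b | Delta method | Percentile bootstrap | Gap (points) |
|---|---|---|---|
| 0.14, 0.14 | 6.2% | 17.1% | 10.9 |
| 0.20, 0.20 | 30.8% | 50.7% | 19.9 |
| 0.22, 0.22 | 43.2% | 63.9% | 20.7 |
| 0.25, 0.25 | 63.7% | 79.5% | 15.8 |
| 0.30, 0.30 | 87.9% | 93.1% | 5.2 |
| 0.39, 0.39 | 98.5% | 99.2% | 0.7 |
| 0.14, 0.39 | 36.8% | 47.0% | 10.2 |
| 0.39, 0.14 | 30.1% | 37.9% | 7.8 |
| 0.20, 0.39 | 67.8% | 75.0% | 7.2 |
| 0.20, 0.59 | 73.1% | 75.2% | 2.1 |
| 0.25, 0.50 | 89.0% | 91.1% | 2.1 |

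Monte Carlo error is about 1 to 2 points per power estimate. A second set-up, with a balanced two-valued exposure, no direct effect and 1,500 trials, gave much the same: 31% vs 52% at 0.20, 44% vs 65% at 0.22, and 63% vs 81% at 0.25.

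The article states no post-randomisation loss; its 15% is "with the expectation that 15% of participants will be unsuitable based on outcomes of the baseline assessment", which falls before randomisation. If 15% were nevertheless lost afterwards (172 × 0.85 ≈ 146), the gaps in the first set-up would run from about 1 to 22 points.

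**5. Rejection when there is no indirect effect.** With one path zero, the other 0.3 and N = 172, the delta-method test rejected in 1.9% to 3.0% of trials across runs, and the percentile bootstrap in 5.3% to 6.9%. With both paths zero the rates were 0 of 1,000 and 0.5%. Part of the power gap thus reflects the delta-method test running below its nominal 5%. The bias-corrected bootstrap rejected in 8.0% to 8.5% under the null.

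**The case against.** The strongest reply is that the article names no default test. A joint-significance test of the two paths would lose essentially nothing (50.7% against 50.7% for the bootstrap at a = b = 0.20), and a condensed article may leave the choice to the analysis plan. If normality meant that of the indirect-effect estimate itself, the rule would already lead to the bootstrap. This stands in part: the delta-method default is an inference, and the power loss is conditional on it. But a rule that switches to the bootstrap when normality is violated most naturally implies normal theory otherwise, and the wording shared with section 2.12 makes the second reading unlikely. A joint test also gives no interval for the indirect effect.

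Second, the harmful branch may seldom be reached. The severity rating is bounded from 0 to 8 (section 2.6), participants are selected for having a diagnosis (section 2.4), and gender is categorical, so a normality check could well fail. That is fair, but it does not defend the rule: if the check always fails the condition is pointless, and if it passes it points away from the better method.

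Third, the simulated model has one mediator, whereas section 2.12.1 lists several intermediate variables. The mechanism carries over to sums of products, but the exact figures need not.

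Two stronger readings are tempting. A reader might infer that the plan loses about 20 points of power outright; that figure is close to the worst case among the settings examined and needs both paths near 0.20 to 0.22. A reader might also infer that a true effect of the enhanced programme through social participation would be reported as absent. The text does not support this: the exposure in section 2.12.1 is baseline severity, and treatment arm does not appear there.

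**Conclusion.** The point holds in a limited form. The rule is stated in the article, so this is not a complaint about missing detail, and it ties inference on the indirect effect to a check that does not establish its validity. If the default is a delta-method test, that test is conservative and loses up to about 20 points of power at N = 172: about 16 to 21 points when both paths are 0.20 to 0.25, about 2 to 10 when they are unequal, and about 1 to 6 when both are 0.30 or more. These figures rest on assumed path sizes, a single mediator, normal data and complete follow-up. The error is a missed indirect path rather than a false claim of efficacy. It touches an explanatory analysis only; the primary comparison and the sample size of 172 are unaffected.

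**What to change.** In section 2.12.1, state that inference for indirect effects will use percentile nonparametric bootstrap confidence intervals, resampling participants, in all cases and regardless of any normality check. Keep the conditional rule, if wanted, for the total and direct effects only. Specify the percentile interval rather than the bias-corrected one, given the null rejection rates above.

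Section 2.12 plans multiple imputation, so the text should also say how the two are combined, for example whether imputation is done within each resample or resampling within each imputed data set.

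The cost is a sentence or two, that one added decision, and extra computing time. The bootstrap is already planned as a fallback, so no new data or change of design is needed.
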